**This is the original document submitted to our national ethics committee before we started this specific study.**

**SPIDIMAN 01 protocol**

Synopsis

Title

Open label single centre randomized cross over study

to validate current algorithms and evaluate safety and efficacy of closed loop insulin delivery (FlorenceD2 system) in children with type 1 diabetes between 6 – 12 years of age

Objectives:

Long Term

Improve and facilitate diabetes management in children with

type 1 diabetes by closing the loop

Short term

- Validation of the algorithms for the overnight closed loop system in children with t1dm between 6-12 y in the clinic and at home. Collect glucose, insulin and insulin infusion rate data, helping to improve future ability of computer–based closed loop algorithms to control blood glucose in children with type 1 diabetes

Primary outcome

- Time spent in normal glucose range (70-144 mg/dl) of the children with type 1 diabetes 6-12 years with the use of an automated overnight closed loop pump uploaded with sensor and automated insulin feedback system without manual intervention overnight in the clinic and at home setting as measured by secondary CGM (start 1800, post dinner bolus, and till pre breakfast bolus 0730),

Secondary outcome (secondary CGM)

- Glucose variability (excursions) when treated with overnight closed loop in the clinic and at home (1800-0730)
- Time spent in hypoglycaemia (<60 mg/dl), as measured by the sensor, in the clinic and at home
- Time spent in hypoglycaemia (<70 mg/dl), as measured by the sensor, in the clinic and at home
- Time spent in hyperglycaemia (>180mg/dl,), as measured by the sensor, in the clinic and at home
- Comparison of the performance of two sensors at different site

Exploratory

- - User evaluation of the overnight closed loop.
  - Gut flora impact on glycaemic variability

Efficacy endpoint:

- Time spent with glucose values between 70-144 mg/dl (sensor measurements by secondary sensor) comparing the nights with and without automated insulin delivery (FlorenceD2 system with closed loop)
- Time spent in normoglycaemia (70-144 mg/ml as observed by blood glucose measurements) comparing the nights with and without automated insulin delivery

Safety endpoint

- Reduction in Time spent in hypoglycaemia as observed by blood glucose measurements during closed versus non closed loop
- Time spent in low glucose measurements (sensors, <60 mg/dl)

and/or perceived hypoglycaemic values during closed and non closed loop in the clinic and at home

Sample size: 12 children completed, 15 to control for potential drop outs and incomplete read-outs.

Inclusion criteria

Age 6- 12 years, with type 1 diabetes mellitus for at least 6 months, with at least CSII for 6 months.

HbA1c <11 % (< 96,72 mmol/mol)

Exclusion criteria

Physical or psychological disease likely to interfere with an appropriate conduct of the study

Current drug therapy knowing to interfere with glucose metabolism

Non type 1 diabetes mellitus

Power calculation:

Not applicable as this is a feasibility study

Principal investigators

- [name] Co principal investigator DECCP
- [name] Co principal investigator DECCP
- [name] Co-investigator
- [name] Co-investigator
- Study Sponsor Spidiman project EU

**Introduction**

Type 1 diabetes mellitus is a chronic disease frequently starting in childhood. (1) Good metabolic control is needed from diagnosis onwards to prevent long-term complications. To achieve a good metabolic control necessitates intensive education, frequent insulin injections and frequent blood glucose controls as well as a careful evaluation of food intake and physical activity. This comprehensive day-to-day management and life long task is challenging for the child and its family and has a major impact on their quality of life. (2, 3)

Hyperglycaemia is the major risk factor for micro and macroangiopathy later in life, stressing the importance of obtaining as fast as possible near normoglycaemia (4).

For a long time the improved metabolic control has been associated with an increase in major hypoglycaemic events. More recent studies suggest that with current education, insulins and insulin pumps a good metabolic control can be obtained without major risk for hypoglycaemic events (5-7). It is evident, however, that once a major hypoglycaemic event has been observed this creates a major anxiety in family and patients, frequently leading to a persistent metabolic deterioration. (8)

Short term and long term complications show the need to improve insulin delivery and glucose control. Continuous subcutaneous insulin infusion (CSII) devices, uploaded with continuous glucose monitoring devices (CGM) are now developed to improve metabolic outcome without further increase of the major burden of child and family (9).

Algorithms either based on mathematical modelling PID (Proportional Integral Derivative), MPC (Model predictive control) or MD fuzzy logic may offer the potential to create an Artificial Pancreas (AP), an automated insulin administration based on the information of CGM (10-12) . Through this technology it should be possible to improve metabolic outcome, without hypoglycaemia and without increased burden for families. First results of this are currently becoming available (13)

We have demonstrated the effect of the sensor-uploaded pump, which still needs patient/parent intervention. In the SWITCH study we could demonstrate a reduced time, spent in hypoglycaemia and a reduction in HbA1c when the sensor was used more than 70 % of the time. (14)

Several studies evaluating the outcome of CSII shows a beneficial impact on quality of control as well as on quality of life. (15,16) Although the sensor uploaded pump was expected to lead to further improvement, this has not (yet) been confirmed with the currently used technology. In the younger child, the presence of two injection sites has been mentioned as a possible contributing negative factor. The development of a single port administration of insulin in combination with glucose measurement through one needle/catheter may be a way forward.

Constant presence and information on the glucose values may as well create extra stress and frustration. This continuous confrontation with the diabetes and the continuous necessity to react to the information provided by the sensor has been suggested to increase the burden and contribute to reduced quality of life.

These observations all point towards the need to move to closed loop systems in which intervention of parents/patients is not requested all the time.

Relevant for the development and use of overnight closed loop systems are its different components, the insulin delivery system, the sensor and its reliable feedback as well as the algorithms, regulating insulin delivery.

CSII (insulin delivery systems) as well as the CGM (Continuous Glucose Monitoring) are currently on the market. Further improvement of this will be obtained in phase two (WP9) of the Spidiman project in which a single port entry will be developed and tested (allowing insulin administration and glucose sensing within 1 needle/catheter).

The sensors, used in this study, are both approved for use in the target group.

Recent studies suggest a potential interaction in some cases with different drugs. (17) This potential effect will be evaluated by documenting the drugs used just before and during the study.

Potential changes in measurements of sensors may as well be caused by the local immune reactions, as well as possible immune stimulation through the gut flora. (18)

One of the major contributions to develop a closed-loop system prototype device has been provided by the research team , Cambridge, UK, led by [name], involved in developing novel Model Predictive Controller (MPC) computer algorithms and research into closed-loop insulin delivery since late 1990s (19-21).

The Model Predictive Control (MPC) algorithm estimates patient-specific parameters from CGM glucose measurements taken every 1 to 15 minutes, makes predictions of glucose excursion and calculates basal insulin infusion rates. The MPC approach can handle delays associated with insulin absorption and takes into account meal intake and prandial boluses delivered manually by the patient. The model representation enables simulation of ‘what if’ scenarios, in particular the prediction of future glucose excursions resulting from projected and past insulin infusion rates.

Overnight closed-loop research conducted in Cambridge, UK has shown significantly better performance with closed-loop insulin delivery compared to usual pump therapy in both children and adults (19,21,22). Meta-analysis of these studies in 17 children and adolescents [13.4 ± 3.6 years] and 24 adults (37.5 ± 9.1 years) on 45 closed-loop (intervention) and 45 usual treatment (insulin pump therapy) visits, shows closed-loop increased the time in target plasma glucose in both children and adolescents (from 40% to 60%, p = .002) and adults (from 50% to 76%, p < .001) compared with conventional insulin pump therapy (23). Additionally, closed-loop reduced the time spent below 3.91 mmol/L and above 8.0 mmol/L, from 4.1% to 2.1% (p = .01) and 33% to 20% (p = .03), respectively. Glycaemic variability, as measured by the SD of plasma glucose, was lower during closed-loop compared with CSII (1.5 versus 2.1 mmol/litre, p = .007).

In this project we propose to analyse these developed algorithms overnight in children between 6-12 years.

FlorenceD2 system

The system is purpose-built and comprises a computational device containing the algorithm and communicating with the study CGM device and the study insulin pump.

The closed-loop system comprises a FreeStyle Navigator II® Continuous Glucose Monitoring (CGM) System (Abbott Diabetes Care, Alameda, CA, USA), DANA Diabecare R subcutaneous insulin pump (SOOIL Development co, Seoul, Korea), and a MPC-based glucose control algorithm running on a laptop PC. The FreeStyle Navigator II® CGM device and DANA Diabecare R subcutaneous insulin pump are CE-marked as stand-alone medical devices. An overview of this proposed automated closed-loop system is given in Figure 1

Figure 1: FlorenceD2 closed-loop system

Portable computer running the MPC algorithm

[figure not shown]

[figure not shown]

Dana insulin pump

Navigator II Transmitter

Navigator Companion

Navigator Companion

Navigator II Receiver

USB cable

Power cable

A second CGM will be used, but not for insulin administration. It is not linked through telecommunication to the controller, but will serve as objective (called secondary) glucose sensor data source and as extra surveillance during the closed loop at home. It will allow as well a comparison with the blood glucose and insulin measurements and observed insulin delivery , which will serve for optimalisation of the algorithms in this age group.

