**Study design and Patient population**

**Design**

Randomised, 2 period cross over, open label trial to assess efficacy and safety of overnight closed-loop control to target insulin delivery versus open loop insulin delivery in children -with type 1 diabetes aged 6 to 12 years in the inpatient setting and at home. Patients will be randomized in equal numbers to one of the two sequences, (group A or B), which differ only with respect to the initial treatment with (A), or without (B) the overnight closed loop. (Figure 2)

Figure 2

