**Protocol**

Details about the visits and sampling procedure are summarised in table 1a and 1b.

After explanations and consent at visit 1 , the child will be randomised to start either with (group A) or without (group B) closed loop during the inpatient stay and 1 successive night at home.

All children will be invited twice for an overnight stay, once with and once without the closed loop system. During both overnight sessions blood samples will be taken for glucose and insulin measurements, to be used for further testing/improvement of algorithms requested for closing the loop by the Cambridge team.

At visit 2 around two weeks before these overnight stays, the family and patient are invited for a training session in the paediatric clinic. During this session, the DANA pump will be explained. Carb counting as well as technical knowledge on the use of this specific pump will be evaluated before going home.

When sufficient knowledge is acquired, the child will change towards the DANA pump ®. In the same session, we will start with a sensor freestyle Navigator

(Abbott ® ).

During the next two weeks prior to the overnight stay, diabetes control will be as usual , but with sensor and study pump .

Sufficient material will be either provided or prescribed (no extra cost for parents nor CNS)

Visit 3 (the day before the overnight stay in the clinic) will be at the clinic or at home. A new sensor (Navigator) will be placed. A second sensor (Dexcom G4 platinum) will be inserted to validate the Navigator glucose measurements, either at home or in the clinic. This sensor DEXCOM will need initial calibration 2 hrs later, requesting its placement before 1800. This visit will be used to evaluate the appropriate use of pump and sensor.

Visit 4 is the inpatient visit, where at Friday around 1600, the patient and parent(s) will come to the research ward.

The insulin catheter will be changed.

A local anaesthetic cream will be applied before the indwelling cannula is inserted for glucose and insulin measurements.

Blood samples will be taken according to the table 2b.

Stool samples will be collected, when produced, and directly frozen in -80°C (dry ice), or cryoshipper and will be transferred to the IBBL, for storage till measurement.

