During the stay in the clinic a meal (content and carb will be decided before to be given at both hospital stays) will be provided in the ward and insulin bolus administration will be done by the parent according to their personal schedule, using the bolus wizard and before the meal. After the meal/bolus the **FlorenceD2 system** will be started in the group with **FlorenceD2 system on**, whereas in the other group their usual nocturnal insulin delivery will be given. A specialised nurse and /or physician will be present during these overnight stays to solve potential questions/problems.

Around 0700 breakfast is planned and in the **FlorenceD2 system on** group, the closed loop control is stopped, and the insulin bolus based on the personal bolus wizard is given followed by breakfast.

For the FlorenceD2 system **off** group, the insulin bolus is given based on the personal bolus wizard, followed by breakfast. Frequent sampling will be continued till 0930 (table 1b, pg16).

Around that time the iv cannula will be removed and the families will go home.

Sensors and pump treatment are maintained and in those randomised for overnight start, the family is invited to use the FlorenceD2 system again at home overnight after the evening bolus and till the next morning before the breakfast bolus. For any problems the dedicated diabetes hotline will be available 24/24 hrs. Training on FlorenceD2 will be provided on Visit 4.

At visit 5 (the Sunday, 24-36 hrs after the overnight stay) the pump catheter will be changed (every 3 days) , the CGM data will be downloaded, the DEXCOM sensor will be removed and one sensor ( Navigator) will not be changed . The FlorenceD2 system will be returned to the clinic and downloaded as well.

Insulin catheter will be changed again on Tuesday/Wednesday and Friday.

During the week the sensors will stay till the Thursday, day when the sensor will be changed. At visit 6, Thursday, (the day before the second overnight stay) , either at home or in the clinic the new sensors will be placed after EMLA.

Visit 7 , on Friday , will be once again in the clinic with an overnight stay with again either closed loop with sampling or control with sampling , and the same protocol will be applied as on visit 4 ( only an exchange of on- off).

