**Visits time Action Questionnaires/Downloads**

V1 Detailed Information on protocol

Consent and randomisation CRF1

V2 -2 wks Training in the outpatient clinic to use the DANA CRF2

pump FFQ

Training to use the sensor Navigator Competency assessment

V3 d0* Change of sensor and adding second sensor, download CSII/CGM

providing EMLA to apply 1,5 hrs prior to the clinic visit V4

V4 d1 Arrival around 1600, Catheter change and

placement of indwelling venous cannula 24hRecall food intake

24h for sampling of insulin – glucose ( details in table 2b) CRF3

Start closed loop (group A) or open loop evaluation (group B)

after dinner (details in table 2b) Download CSII/CGM

When needed explanation to the family the handling of the

closed loop system (A)

d2 Closed loop (A) starting after dinner at home, stop next Download CSII/CGM°

morning before breakfast

V5 d3 Return FlorenceD2 closed loop system material Download CSII/CGM Change catheter CRF3.2

Problems encountered User Quality of Care1 Evaluation

d5 Change catheter at home (D5 or d6) Phone contact/Home/clinic visit

V6 d7* New sensors (dexcom/navigator) Download CSII/CGM

providing EMLA to apply 1,5 hrs prior to the clinic visit V7

V7 d8 Arrival around 1600 , change catheter ,

placement of indwelling venous cannula 24h Recall foodintake

for sampling of insulin – glucose ( details in table 2b) Download CSII/CGM

Start closed loop (B) or open loop (A) evaluation after dinner CRF3.3

(details in table 2b)

When needed explanation to the family the handling of the

closed loop system (B)

d9 Closed loop (B) starting after dinner at home, stop next Download CSII/CGM°  morning before breakfast

V8 d10 Change back to previous system Download CSII/CGM

Return AP CAM material CRF3.4

Discuss Problems encountered User Quality of Care evaluation

. .

Table 1b Sequence of the procedure

| Time | ACTION/meals and snacks | Plasma glucose | Plasma  insulin | CGM | CSII | BOLUS |
| --- | --- | --- | --- | --- | --- | --- |
| 1630 | Arrival at clinic  Canulation |  |  | X | X |  |
| 1700 | Start sampling | x | x | X | x |  |
| 1800 | Meal | x | x | X | x | X |
| 1830 | Start closed loop (A)  explain, training on starting and stopping closed loop start | x | x | X | x |  |
| 1900 | Play | X | x | X | x |  |
| 1930 | Play | x | x | X | x |  |
| 20.00 | Time for bed | x | x | X | x |  |
| 2100 | Lights out | x | x | X | x |  |
| 2200 |  | x | x | X | x |  |
| 2300 |  | x | x | X | x |  |

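### The sensor that scores the outcome is given a surveillance role for closed-loop home nights only, and the protocol does not say it is handled the same way on control home nights

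*Protocol*

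**What the plan says.** The FlorenceD2 system subsection of the Introduction describes a second CGM that is not connected to the controller. It gives that sensor two jobs: it "will serve as objective (called secondary) glucose sensor data source and as extra surveillance during the closed loop at home".

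The Synopsis makes this sensor the primary-outcome instrument, for automated delivery "without manual intervention overnight in the clinic and at home setting as measured by secondary CGM", over a window given as "start 1800, post dinner bolus, and till pre breakfast bolus 0730". The secondary outcomes, including time below 60 and below 70 mg/dl in the clinic and at home, are also placed under the secondary CGM.

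The sensor is worn in both conditions. For period 1 the Protocol section says "A second sensor (Dexcom G4 platinum) will be inserted to validate the Navigator glucose measurements", with no restriction to one group, and for the home night "Sensors and pump treatment are maintained". For period 2, Table 1a lists "New sensors (dexcom/navigator" at visit 6, again for everyone.

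The Design section says the two sequences are ones "which differ only with respect to the initial treatment with (A), or without (B) the overnight closed loop". The trial is open label. Under Data analysis, only the person analysing the data is blinded.

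**The concern.** Surveillance has a purpose only if someone may respond to it. The protocol attaches it to one of the two conditions being compared, and to the device that scores the comparison. If a low reading on the second CGM leads to food or to stopping the loop on a closed-loop home night, and the same reading would go unseen on a control home night, the recorded difference mixes the algorithm with the extra watching. Blinding the analyst does nothing about behaviour at home.

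The protocol's own background supports the mechanism. The Introduction reports less time in hypoglycaemia with a sensor-linked pump that still relied on patient or parent action, and it describes families' need to keep reacting to sensor information.

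At stake is the home hypoglycaemia comparison, which appears among both the secondary outcomes and the safety endpoints.

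**Working it through.** **Passages side by side.**

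- Surveillance by the second CGM is named for closed loop at home. No section names it for control nights, masks the sensor, or says who watches it or acts on it.
- The primary-outcome wording excludes manual intervention overnight. It can be read as describing insulin delivery alone, but the protocol does not say so, and a response to surveillance is hard to fit under it.
- The Design section presents the order of closed loop as the only difference between sequences. Condition-specific surveillance would be a second difference between the two home nights.

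**What the planned records would show.** Pump and CGM downloads follow both home nights (Table 1a), FlorenceD2 is downloaded at visit 5, and CRF3 asks for boluses in the preceding 24 h. Boluses and loop stops should therefore be recoverable. Food is the gap: the 24-h food recall is listed at visits 4 and 7 but not at visits 5 and 8, which follow the home nights. CRF3 counts only severe events and has no field for an action prompted by a sensor.

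**Size.** The protocol states no figure for this and has no power calculation, so there is nothing to reproduce. What follows is a sensitivity calculation.

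Inputs from the protocol:
- Window 1800 to 0730 = 13.5 h × 60 = 810 min (Synopsis).
- Cited time below 3.91 mmol/L: 4.1% without and 2.1% with closed loop (Introduction).
- Cited time in target, children and adolescents: 40% and 60% (Introduction).
- 12 completers (Synopsis).

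Cited effects, if they applied to this window:
- Hypoglycaemia: 0.041 × 810 = 33.2 min; 0.021 × 810 = 17.0 min; difference 16.2 min (2.0 points).
- Time in target: 0.40 × 810 = 324 min; 0.60 × 810 = 486 min; difference 162 min (20 points).

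Assumption, not in the protocol: on a fraction f of closed-loop home nights, surveillance shifts m minutes of glucose across the relevant threshold. Then

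mean shift in points = 100 × f × m / 810.

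| f | m (min) | Shift (points) | Share of 2.0-point hypoglycaemia effect | Share of 20-point time-in-target effect |
|---|---|---|---|---|
| 10% | 15 | 0.19 | 9% | 0.9% |
| 25% | 30 | 0.93 | 46% | 4.6% |
| 50% | 30 | 1.85 | 93% | 9.3% |
| 100% | 60 | 7.41 | 370% | 37% |

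The last row is a limit of the arithmetic, not an expectation: 60 min saved every night exceeds the 33.2 min of low time in the cited control figure.

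A single event is small. One saving of 15 to 20 min in one of 12 children moves the mean by 15/12 = 1.25 to 20/12 = 1.67 min, which is 8% to 10% of 16.2 min.

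**The case against.** The strongest reply is that the asymmetry is read from silence. The protocol does not restrict surveillance to closed-loop nights in so many words, and it does not say that families do the watching or that alarms differ between nights. The second sensor and the Navigator are worn in both conditions. A trained team is available throughout the study, and "For any problems the dedicated diabetes hotline will be available 24/24 hrs". Control nights are therefore not unmonitored, and parents giving usual care may act then too. Extra watching of an investigational system in children at home is also a legitimate safety measure, and this is a feasibility study.

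Most of this stands, and it limits the point. A reader might infer that control nights have no surveillance, that the home results are biased, or that the bias favours closed loop. The protocol supports none of these. Differential action is neither stated nor excluded. A loop stop or an unneeded snack could lower closed-loop time in range, and action by parents on control nights could work against closed loop. A reader might also infer that one treated low would cancel the expected benefit; the 16.2 min is a mean per night, so it would not.

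What the reply does not remove is that the words limiting surveillance to closed loop at home are the protocol's own. Wearing the same sensor on both nights does not make its use the same on both.

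**Conclusion.** The point holds as a gap in design control, not as demonstrated bias. The plan as written permits surveillance through the outcome sensor on one of the two home nights being compared, and food given in response would not be systematically recorded.

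Home time below 60 and 70 mg/dl is sensitive to this: modest assumed action (30 min on 25% of closed-loop home nights) amounts to about 46% of the cited effect. Home time in range is much less sensitive, at about 5% of the cited effect under the same assumption. The surveillance role does not extend to the clinic nights.

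These sizes rest on assumed values of f and m. They also rest on cited effects that are plasma-glucose results from other studies, whose time windows are not given; the hypoglycaemia threshold there was 3.91 mmol/L. The point deserves correction at moderate priority.

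**What to change.** 1. State that the display, alarm and surveillance handling of the second CGM is the same on closed-loop and control home nights. The level is for the clinical team to choose. If a difference is to remain, describe it, so that the home comparison is read as closed loop plus that surveillance.
2. Record on both home nights any action prompted by a sensor, including food, with the clock time, and collect the record at visits 5 and 8.
3. Reconcile three places: the primary-outcome wording on manual intervention (Synopsis), the surveillance role (FlorenceD2 system), and the statement of how the sequences differ (Design).

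The cost is a sentence or two of text, the same device set-up on both home nights and a short log. Families carry that set-up and log on the control night too. Equal settings will not mean equally frequent alerts, since those depend on glucose. No extra device or staff is needed.
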